### Interim analyses

An interim analysis will take place 3 year after randomization of the last patient in the trial.

## Oversight and monitoring

### Data monitoring

To ensure that the trial is performed according to the protocol—that the data is collected, documented, and reported according to ICH-GCP as well as regarding ethical and regulatory requirements—the trial will be monitored by an independent monitor before the start of the trial, during the course of the trial, and after the trial ends, through Karolinska Trial Alliance. This will take place according to the monitoring plan for the trial and aims to ensure the rights, safety, and well-being of participants as well as to oversee that data in the CRF forms is filled in correctly.

### Harm

#### Registration of events

An AE is defined as any unfavorable event or worsening of an existing medical state in a subject that receives a trial medication, regardless of causation. An SAE is a serious event where a specific dose leads to death, is life-threatening, requires health care, causes remaining or massive invalidation or disability, or causes an abnormality or malformation. A SUSAR is defined as a side effect or an incident that is serious, unexpected, and suspected to be caused by the treatment. Subjects will be encouraged to contact the principal investigator if any of these incidents occur. They will also be specifically asked about AE, SAE, and SUSAR after 1 month of treatment and at regular follow-ups throughout the course of the trial. All AE will be registered in the CRF and evaluated regarding causation, intensity, and if the incident is classified as an AE or an SAE. SAE will be reported in a specific form and submitted to the principal investigator within a day. SUSAR will be evaluated by a licensed physician and further reported to The Swedish Medical Products Agency and the physicians that have met the subject during check-ups. Lethal or life-threatening SUSAR will be reported within a week and complemented with other relevant information within the 8 days following, while other types of SUSAR will be reported within 15 days.

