#### Intervention

Participants will be equally randomized into two groups: the melatonin group (treated with 20-mg melatonin each night for 5 years) or the control group (no intervention). When a patient is recruited and randomized to the melatonin group, blood samples will be ordered by a licensed physician regarding creatinine, electrolytes (sodium, potassium), and alanine transaminase (ALAT). This blood test will be repeated after 2 and 4 years (Fig. 1 and Tables 1 and 2).

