### Outcomes

The primary outcome is the number of patients which develop metastasis in the melatonin group vs. the control group. This will be evaluated as a relative risk (RR), with a 95% confidence interval. The secondary outcomes include the following: Overall survival 5 years from randomization in the melatonin group vs. control group, evaluated with Kaplan-Meier curves and the Log-rank test.Overall survival after detection of metastases in the melatonin group vs. control group, was evaluated with Kaplan-Meier curves and the Log-rank test.Hazard for having developed other cancers within 5 years from randomization in the melatonin group vs. control group, evaluated as Cox regression hazard ratio (HR).Number of patients with AE and SAE in the melatonin group vs. control group, assessed by CTCAE and evaluated as relative risk (RR) with a 95% confidence interval.

Other outcome measures:Interim analysis: number of patients developing metastasis within 3 years in the melatonin group vs. control group, evaluated as relative risk (RR), with 95% confidence interval.Interim analysis: overall survival in 3 years in the melatonin group vs. control group, evaluated with Kaplan-Meier curves and the Log-rank test.

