#### Clinical safety

Our outcomes for clinical safety will be the number of adverse events (AE), the number of serious adverse events (SAE), and the number of suspected unexpected serious adverse reactions (SUSAR) in the melatonin group and control group respectively. These will be measured through data collected from CRF forms and patients’ chart documentations. The subjects are encouraged to contact us if they experience side effects, or new or worsened symptoms. They will be asked about AE and SAE at 3 months and 1 year after starting melatonin treatment, and thereafter every 6 months until 5 years have passed since recruitment.

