#### Evaluation of events

The principal investigator will evaluate the possible causation between AE/SAE and melatonin usage. If such an association is found, the subjects will be followed until declared healthy, until a “near healthy” status is declared, or until the principal investigator considers no further need for follow-up. All AE/SAE will be categorized as probably related, possibly related, or not related. Probably related events are defined as clinical events, including abnormal laboratory analysis results occurring at a reasonable time following melatonin administration, if the event is unlikely to be related to an underlying disease or another medication, or if the symptoms are previously known side effects of melatonin. Possibly related events are defined as clinical events, including abnormal laboratory analysis results occurring after a reasonable time following melatonin treatment, where the event can be explained by the usage of melatonin, but there is not sufficient information to ensure the causation exists. Not related events are defined as clinical events including abnormal laboratory analysis results occurring at an unreasonable time as related to melatonin treatment, thereby suggesting the event is likely not related to the intervention (melatonin) and can be explained by another medication or underlying disease.

Unfavorable medical events will be classified and graded according to the Common Terminology Criteria for Adverse Events (CTCAE), version 5.0. based on the following:

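### AE and SAE are defined only through trial medication or dose, and blood tests are tied in the text to the melatonin arm, so the planned between-arm AE/SAE ratio cannot be computed as defined and may be ascertained unequally

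*Protocol article*

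**What the plan says.** The Outcomes section of the protocol article lists as a secondary outcome "Number of patients with AE and SAE in the melatonin group vs. control group", graded by CTCAE and expressed as a relative risk with a 95% confidence interval. Study objectives and hypothesis names the same comparison as a secondary objective. Clinical safety plans AE, SAE and SUSAR counts "in the melatonin group and control group respectively".

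The definitions are under Harm, Registration of events. For AE: "An AE is defined as any unfavorable event or worsening of an existing medical state in a subject that receives a trial medication", whatever the cause. For SAE: "An SAE is a serious event where a specific dose leads to death, is life-threatening, requires health care", followed by further criteria. Trial design says there is no placebo, and Intervention describes the control group as having no intervention.

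On laboratory tests, Intervention says: "When a patient is recruited and randomized to the melatonin group, blood samples will be ordered by a licensed physician". The tests are creatinine, sodium, potassium and ALAT, repeated at years 2 and 4. Tables 1 and 2 show blood tests at the same times without naming an arm. Evaluation of events describes its relatedness categories as covering "clinical events, including abnormal laboratory analysis results".

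On timing, Clinical safety says: "They will be asked about AE and SAE at 3 months and 1 year after starting melatonin treatment", then every 6 months. Follow-up and Tables 1 and 2 give 1 month and then every 6 months. Registration of events also gives 1 month, counted from treatment.

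**The concern.** A between-arm ratio needs one event definition that can be met in both arms and the same opportunity to find events in both arms. The article departs from this in three places.

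- **Definition.** The AE definition requires trial medication and the SAE definition requires a dose. A control has neither. Staff who follow the text record nothing for controls. Staff who do record control events must make up their own rule, in a trial where they know the allocation.
- **Ascertainment.** If blood is drawn by protocol in one arm only and abnormal results are events, that arm gains events that the other has little chance of showing.
- **Timing.** Two different first-year question schedules are stated, and one starts its clock at an event that controls never have.

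At stake is the trial's only comparative safety result. The Discussion notes that most of the year-long studies it cites at this dose took no tests for subclinical adverse events, so this comparison carries real weight.

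**Working it through.** **1. The plan's own figure.** The article gives no expected AE or SAE rates. Its only design figure is 42 per group for 30% v 60% metastases, two-sided alpha 0.05, power 80%. It reproduces: n = [1.96 × √(2 × 0.45 × 0.55) + 0.842 × √(0.3 × 0.7 + 0.6 × 0.4)]² / 0.3² = 42 after rounding up. It is not in dispute. The 30% and 60% are used in step 5.

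**2. Literal definition.** With 50 per arm and *a* melatonin patients with an AE, RR = (*a*/50) / (0/50). The denominator is zero by construction, so no relative risk or confidence interval exists. The same holds for SAE.

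**3. Does the rest of the text follow that definition?** It does not. Follow-up has participants telephoned every 6 months. Tables 1 and 2 list AE/SAE questions with no arm limit. Evaluation of events has a not-related category for events explained by other medication or underlying disease, which would be unnecessary if every SAE had to follow from a dose. So the definition contradicts the intended collection.

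**4. One-arm blood tests (illustration).** From the article: two post-baseline draws (years 2 and 4). Assumed: a clinical AE rate *a*, the same in both arms; a probability *q* that a draw gives an abnormal result recorded as an AE; independence; no laboratory events in controls.

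Melatonin rate = 1 − (1 − *a*)(1 − *q*)²; control rate = *a*.

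| *a* | *q* = 5% | *q* = 10% | *q* = 20% |
|---|---|---|---|
| 10% | 0.188, RR 1.88 | 0.271, RR 2.71 | 0.424, RR 4.24 |
| 30% | 0.368, RR 1.23 | 0.433, RR 1.44 | 0.552, RR 1.84 |
| 50% | 0.549, RR 1.10 | 0.595, RR 1.19 | 0.680, RR 1.36 |

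Every entry is above 1 although melatonin has no effect on AEs.

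**5. What happens once the dose clause is removed (illustration).** Without it, metastasis could meet the remaining SAE criteria, because In the event of detection of metastases describes referral and systemic treatment. Assume that every metastasis then counts as an SAE, and that other SAEs occur at rate *b* independently of metastasis and equally in both arms. With *b* = 10%:

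- Melatonin: 1 − 0.7 × 0.9 = 0.37
- Control: 1 − 0.4 × 0.9 = 0.64
- RR = 0.37/0.64 = 0.58, with no toxicity difference

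If melatonin doubled other SAEs to 20%, the melatonin rate would be 1 − 0.7 × 0.8 = 0.44 and the RR 0.44/0.64 = 0.69, still below 1.

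**6. Question schedules over the first year.**

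| Source | Contacts | Stated clock |
|---|---|---|
| Clinical safety | 3 months, 1 year | start of melatonin |
| Follow-up | 1 month, then every 6 months | recruitment |
| Tables 1 and 2 | 1, 6, 12 months | trial visits |
| Registration of events | 1 month, then regular follow-ups | start of treatment |

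From year 1 the stated intervals agree at 6 months.

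**The case against.** The strongest reply is that a zero control count is a literalism. The objectives, outcomes, tables and telephone calls all show that events are to be collected in both arms, so in practice a ratio would be produced. That stands as a description of intent, and it rules out saying that the whole safety collection is invalid. It does not rescue the definition, which staff and monitors are meant to apply as written.

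On blood tests, the tables name no arm, so one-arm sampling is not established. Equally, Table 1 lists prescribing melatonin in the same column, so the tables do not show that controls are sampled. Clinical safety also draws on patient charts, so controls could have laboratory findings from routine care; this would reduce the bias in step 4 without removing it.

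The schedule conflict is confined to the first year, and the Clinical safety sentence ends its 5-year span at time since recruitment. It is a small inconsistency.

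Two stronger readings are tempting. A reader might infer that the SAE definition already includes the cancer outcome. No section says so, and none excludes it. The dose clause and the Grade 5 wording, which refers to death from side effects, point away from it; the underlying-disease ground for not-related events points towards it. The full protocol may settle this. A reader might also infer that ALAT testing in one arm brings forward the detection of metastases. Nothing links ALAT to extra imaging, and all patients have liver imaging every 6 months, including at the year 2 and 4 visits when blood is drawn.

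**Conclusion.** The point holds for the definitions, the blood-test text and the question schedule. As written, the AE and SAE definitions conflict with the planned between-arm comparison and, followed literally, leave a relative risk that cannot be estimated. This part needs no assumed rates.

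The laboratory part is conditional. If only the melatonin arm is sampled, the AE ratio is biased against melatonin. The size depends on assumed rates: 1.23 to 1.84 at a 30% clinical AE rate, and 1.10 to 4.24 over the whole grid shown.

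The SAE figure of 0.58 describes a risk that arises when the dose clause is corrected and melanoma events are left unaddressed. It is not a property of the present text. It rests on the plan's 30% and 60%, an assumed 10% background rate, and every metastasis counting as an SAE. Since the two illustrations run in opposite directions, no net direction is claimed.

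Severity is should-fix: a secondary outcome is affected and the primary outcome is not.

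**What to change.** 1. In Registration of events, define AE and SAE for every randomised participant from randomisation, with seriousness tied to the event and not to a dose.
2. In the same edit, state that uveal-melanoma metastasis and death from it are reported as efficacy outcomes and left out of the between-arm SAE ratio.
3. Reconcile the Intervention section with Tables 1 and 2 on which arm has blood tests. If only one arm is sampled, leave abnormalities found solely by protocol blood tests out of the AE ratio and report them separately.
4. Reconcile Clinical safety with Follow-up, Registration of events and the tables, so that one AE question schedule, counted from randomisation, applies in both arms.

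The cost is a protocol amendment and matching CRF wording. No additional staff are needed, since the calls and tests are already listed. It is best done early, because changing event definitions after open-label data have accrued would be less credible.

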**Table Tabb:** 

Grade 1:	Mild Asymptomatic or mild symptoms Only clinical or diagnostic observations; intervention not indicated
Grade 2:	Moderate Minimal, local, or non-invasive interventions indicated; affects age-adjusted ADL
Grade 3:	Severe Medically significant but not acutely life-threatening; hospitalization or lengthened health care indicated; disabling; limits personal ADL
Grade 4:	Life-threatening Life-threatening consequences, acute interventions indicated
Grade 5:	Death related to side effects

In urgent situations, the principal investigator will immediately take urgent safety measurements required to protect the subjects, such as temporarily terminating the clinical trial medication or implementing additional monitoring measures. An overdose of medication associated with AE will be registered as a diagnosis or symptom in the CRF, and in the subject’s journal documentation if no associated symptoms are found. Women of fertile age will be excluded from this trial.

All study participants will be insured via LÖF (the Swedish patient insurance).

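### The seriousness criterion is not limited to hospital care, and the safety comparison is a patient-level any-AE relative risk that is open to a ceiling, ignores time at risk and conflicts in its unit with another section

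*Protocol article*

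**What the plan says.** Four parts of the protocol article bear on this.

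- **Registration of events (under Harm)** defines the terms. On AEs: "An AE is defined as any unfavorable event or worsening of an existing medical state in a subject that receives a trial medication", whatever the cause. A serious event counts as an SAE if a particular dose causes death, puts life at risk or "requires health care, causes remaining or massive invalidation or disability"; malformation is listed as well. Hospital admission is not mentioned.
- **Evaluation of events** adds grading: "Unfavorable medical events will be classified and graded according to the Common Terminology Criteria for Adverse Events (CTCAE), version 5.0". In the grade table, grade 2 already covers events for which a minimal, local or non-invasive intervention is indicated. Hospital care appears only at grade 3: "Medically significant but not acutely life-threatening; hospitalization or lengthened health care indicated; disabling; limits personal ADL".
- **Outcomes** states the secondary safety outcome as "Number of patients with AE and SAE in the melatonin group vs. control group, assessed by CTCAE and evaluated as relative risk (RR"). Its confidence interval is to be at the 95% level. It sets no threshold for grade or relatedness.
- **Clinical safety** states it differently: "Our outcomes for clinical safety will be the number of adverse events (AE), the number of serious adverse events (SAE"), together with the number of SUSARs, in each group. Collection runs until 5 years after recruitment.

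Comparing AE and SAE occurrence between the groups is also a named secondary objective (Study objectives and hypothesis).

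**The concern.** Three features of the wording weaken the safety comparison.

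1. **The seriousness criterion is loose.** An event that needs only an outpatient visit or a prescription can be read as needing health care. A moderate, grade 2 event could then be recorded as an SAE by one assessor and as an AE by another. The classification feeds the SAE form due within a day, the pool of possible SUSARs and the SAE comparison itself.
2. **The unit conflicts.** The number of patients with an event and the number of events are different quantities. A relative risk with a confidence interval suits the first but does not summarise recurrent events.
3. **The patient-level measure uses little of the information.** Once a patient has had one AE of any grade and cause, later or worse events add nothing. If most controls have had one by 5 years, the relative risk has little room to rise above 1 even if melatonin causes many more events. The measure also ignores time at risk. Data collection stops at withdrawal, and patients die. If melatonin prolongs survival, its patients are observed for longer, so the same event rate yields a higher proportion with an AE.

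A relative risk close to 1 could therefore be taken as reassurance about 5 years of treatment when the measure could not have shown much else.

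**Working it through.** **The seriousness criterion, by comparing the texts.** The SAE definition requires a need for health care and sets no level of care. The grade table separates care that is minimal, local or non-invasive (grade 2) from hospital or lengthened care (grade 3). A grade 2 event that is treated meets the SAE phrase as worded but falls below the grade table's own line for hospital care. The two texts do not mark the same boundary.

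**The unit.** Outcomes counts patients and Clinical safety counts events. Neither section says which is the comparison and which is supplementary.

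**The ceiling: inputs.** From the protocol: 5 years of follow-up, 50 per arm, two-sided alpha 0.05, chi-square test. Not in the protocol: any AE rate. The annual control rates r below are assumptions, as is a doubling on melatonin.

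**Check of the power formula on the plan's own figure.** For 30% v 60%, with mean proportion 0.45 and 80% power:

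n = [1.96 × √(2 × 0.45 × 0.55) + 0.842 × √(0.3 × 0.7 + 0.6 × 0.4)]² / 0.30² = 41.97, so 42 per arm.

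This matches the Sample size section. The same normal approximation is used below.

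**Formulas.**
- Share of controls with at least one AE: p0 = 1 − exp(−5r). With a doubled rate on melatonin: p1 = 1 − exp(−10r).
- Largest possible relative risk: 1/p0.
- Power = Φ{[(p1 − p0)√50 − 1.96√(2p̄(1 − p̄))] / √(p1(1 − p1) + p0(1 − p0))}, where p̄ is the mean of p0 and p1.

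| Assumed control rate per year | Control with any AE | Melatonin with any AE | RR | Maximum RR | Power |
|---|---|---|---|---|---|
| 0.1 | 39.3% | 63.2% | 1.61 | 2.54 | 67% |
| 0.2 | 63.2% | 86.5% | 1.37 | 1.58 | 77% |
| 0.3 | 77.7% | 95.0% | 1.22 | 1.29 | 72% |
| 0.5 | 91.8% | 99.3% | 1.08 | 1.09 | 45% |
| 1.0 | 99.3% | 99.995% | 1.007 | 1.007 | 8% |

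The true rate ratio is 2 in every row. The normal approximation is poor in the last row and overstates the power. Significance there needs at least 4 event-free controls out of 50, when the expected number is 50 × exp(−5) = 0.34. The exact binomial power is below 0.1%.

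**Where significance becomes impossible.** Suppose all 50 melatonin patients have an AE. The uncorrected chi-square for 50/50 v x/50 is 100(50 − x)² / [(50 + x)(50 − x)] = 100(50 − x)/(50 + x).
- x = 46: 400/96 = 4.17, p = 0.041.
- x = 47: 300/97 = 3.09, p = 0.079.

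So from 47 of 50 controls (94%) upward, no result in the melatonin arm can be significantly worse.

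**SAEs.** The protocol gives no SAE rate either. If metastases counted as SAEs, its own assumption of 30% v 60% gives RR 0.50 with 87% power at 50 per arm. Add an other-cause SAE risk q, equal in both arms and independent of metastasis. The proportions become 1 − 0.7(1 − q) and 1 − 0.4(1 − q). At q = 0.3 they are 51% and 72%; at q = 0.9 they are 93% and 96%. Both arms come near 100% only if q is about 0.8 to 0.9.

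**The case against.** A reader might infer that both the AE and the SAE proportions must approach 100%, so that the relative risk cannot show a difference. The documents do not support that. No AE or SAE rate is given, the Discussion reports few side effects in earlier studies, and AEs are elicited by telephone about every 6 months. At assumed control rates of 0.1 to 0.3 per year, a doubling is detected with reasonable power. At 0.5 per year a significant result is still possible. For SAEs, saturation would need a very high other-cause risk that nothing in the protocol indicates.

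It can also be said that the SAE sentence starts from an event that is already serious and ties it to a dose, and that the grade 3 wording suggests inpatient care was meant. That makes loose drafting likelier than a deliberately low threshold. But the phrase still stands as a listed criterion, and assessors will apply what is written.

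The definitions, read strictly, cover only people who receive trial medication, which would leave controls with no events at all. That is a separate drafting matter. The relative risk in Outcomes needs control events to be counted, and the ceiling calculation assumes that they are.

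Finally, event counts, CTCAE grade and relatedness are all recorded, and detailed safety tables commonly belong in an analysis plan. This limits the harm, because the data can be recovered. It does not repair the comparison that the protocol does state, nor the conflict over its unit.

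**Conclusion.** The point holds in a limited form. Two parts rest on the text alone: the seriousness criterion has no inpatient threshold and does not line up with the protocol's own grade table, and Outcomes and Clinical safety use different units. The third part is a vulnerability whose size depends on an unknown rate. The any-grade, any-cause patient-level relative risk loses power as the control proportion rises. For a true doubling, power is about 67% to 77% at control proportions of 39% to 78%, 45% at 92%, and 8% or less at 99.3%. No significant excess is possible from 47 of 50 controls upward.

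These figures assume a constant event rate, the same for every patient in an arm, a full 5 years of observation for all 50 per arm, and events counted in both arms. Shorter observation through death or withdrawal would lower the proportions and ease the ceiling, but would bring in the unequal time at risk that the relative risk ignores. Saturation of SAEs is not shown. The primary outcome is not affected.

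**What to change.** - In Registration of events, restate the criterion as an event that requires or prolongs hospital inpatient care, consistent with the protocol's own grade 3 text.
- Reconcile Outcomes and Clinical safety on the unit, stating which quantity is compared between arms.
- Make the between-arm comparison the proportion of patients with a CTCAE grade 3 or higher event and the proportion with an SAE, together with AE rates per patient-year. The rates use the event counts and account for different observation time.
- Keep the number of patients with any AE of any grade as a descriptive figure.

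The cost is a change of wording and a slightly longer safety table. Grades and events are already recorded, so no new data are needed.
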